|   |                                                                                                                                                                                        |                          | 1.2.7     | Cardiac arrest during intervention                            | Utstein definition (13)                                                       |  |
|   |                                                                                                                                                                                        |                          | 1.2.8     | GOS-E score on day 28                                         | GOS-E: Glasgow Outcome Score Extended                                         |  |
|   |                                                                                                                                                                                        | 1.2.9                    | Mortality | 24 hour and 28 days                                           |                                                                               |  |
|   | Secondary                                                                                                                                                                              |                          |           | Secondary                                                     |                                                                               |  |
| 2 | Evaluate the safety of the intervention as compared to the control as assed by:                                                                                                        | 2.1 Circulatory function | 2.1.1     | Heart rate at $t_0\text{-}t_n$                                | Actual HR at time point                                                       |  |
|   |                                                                                                                                                                                        |                          | 2.1.2     | Blood pressure at $t_0$ to $t_n$                              | Invasive or non-invasive. Actual BP at time point                             |  |

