#### **Intervention Duration:**

Estimated one hour but will differ significantly due to the prehospital environment. From inclusion to handing over care time will depend on evacuation and transport times.

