### 5.3 Dosage and Drug Administration

In this trial we follow the SPC of INOMax and start dosing at 20 ppm. We will not allow doses above this within this protocol. Weaning will follow standard practice. The duration of treatment is significantly lower than with the SPC, due to the objective of the trial- increased oxygen saturation prior to RSI

After 3 minutes on standard treatment (O2 12l/min + 10 cm H2O PEEP) patients with a SpO2 between 50 and 90% will be randomized. For patients randomized to O2 + Inhaled nitric oxide the drug will be administered in the following way:

- INOMax 800 ppm mol/mol will be administered by the INOBlender (IMP) at 20 ppm by bag-mask ventilation. O2 and PEEP is continued as per standard treatment. If inadequate spontaneous breathing, the doctor should use the bag to support ventilation in accordance with existing guideline. INOMax at the dose of 20 ppm will be delivered for 5 minutes before any attempt to intubate (or decision not to) will be made.

- After 5 minutes RSI may be performed at the discretion of the study doctor in accordance with departmental procedure for RSI in this category of patients.
- Following RSI, the ventilation bag is squeezed the 3-4 times with O2 / INO before starting ventilation. This is to empty the bag of any NO2 that may have been built up.
- Regardless whether RSI is performed, or bag/mask ventilation is continued, a dose reduction of iNO should be attempted if SpO2 ≥ 94% after 5 minutes (t1)
- Reduction is made in steps of 5 ppm every 5 minutes unless SpO2 drops by > 5 percentage points from the value at t1.
- In case weaning is completed during transportation, self-expandable bag ventilation may be substituted with a mechanical ventilator.
- After arrival in hospital, when patient is intubated, or a decision not to intubate has been made, iNO administered by INOBlender should be weaned by 5 ppm every 5 minutes. In the unlikely event of a rebound effect (as assessed by the study doctor) iNO may be continued temporarily as necessary. INO administered by other devices (i.e.: not IMP) may be initiated as per local routines at the discretion of the attending doctor taking over the responsibility for the patient.

The total duration and concentration of IMP the patient has received will be recorded in the CRF.

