### 6.1.2 Treatment

The doctor's assistant, who is specifically trained for the procedure, will open a sealed envelope with information on patient allocation, and either open or leave the INO cylinder closed accordingly. If randomized to only O2 a simulated cylinder opening will be undertaken. Regardless of randomization the INOBlender is set to deliver 20 ppm. SpO2 is recorded at time of allocation ( $t_0$ ) and after 5 minutes ( $t_1$ ). Other vital signs are automatically and continuously recorded in the internal memory of the patient monitor and extracted at 5 minute intervals to EOI ( $t_0$  to  $t_n$ ).

If the patient is included outside hospital, the doctor makes the decision to either perform RSI prior to transportation or continue current treatment during transport to hospital.

At the time the clinician decides to perform RSI, the lowest SpO2 during the RSI-procedure is recorded ( $t_{RSI}$ ) regardless of where the procedure is performed.

In any event where the bag/mask/valve is left idle, four normal tidal volumes must be ventilated into free air before re-connected to patient in order to purge the system of any NO2 build up.

Blood samples, physiological data and clinical scoring made after EOI is done as indicated by local routines regardless of the study. Relevant clinical data is retrieved from the institution's patient journal on follow-up at day 28 post admission.

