### 6.1.3 End of Intervention

End of intervention is defined as the time point where INO administered by the INOBlender is discontinued.

This may be on different time points before transport, during transport or in hospital. For patients still requiring INO, the receiving hospital INO must be delivered by another INO device, and is no longer defined as IMP.

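### Endpoints 1.2.4 (SpO2 below 50) and 1.2.7 (cardiac arrest) are counted only to End of Intervention, a time that depends on the SpO2 response, so the better-responding arm tends to be observed for less time.

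*Protocol*

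**What the plan says.** Section 6.1.3 fixes End of Intervention (EOI) by exposure: "End of intervention is defined as the time point where INO administered by the INOBlender is discontinued". It adds: "This may be on different time points before transport, during transport or in hospital".

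Section 5.3 makes that time depend on oxygenation. At t1, "a dose reduction of iNO should be attempted if SpO 2 ≥ 94% after 5 minutes". The steps and their brake follow: "Reduction is made in steps of 5 ppm every 5 minutes unless SpO 2 drops by > 5 percentage points from the value at t" (the last symbol is t1, the five-minute reading). The same section foresees that weaning may be completed during transport. Patients not weaned on the way are weaned after arrival in hospital, once they are intubated or a decision against intubation has been made. Section 3 gives the duration as "Estimated one hour but will differ significantly due to the prehospital environment".

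In section 2, endpoint 1.2.4 is the number of patients with SpO2 below 50 from t1 to EOI, and 1.2.7 is "Cardiac arrest during intervention". Under section 6.1.2 the monitor records vital signs continuously, but they are "extracted at 5 minute intervals to EOI". Section 10.5 assigns binary endpoints to logistic regression.

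**The concern.** Both endpoints are yes/no counts, and the length of the counting period is decided after randomization by SpO2 at five minutes. Raising SpO2 is the purpose of the drug, so an arm with more patients at 94% or above will tend to have a shorter average window. Blinding does not prevent this, because the rule acts on the oximeter reading and not on knowledge of allocation. A logistic regression that ignores time at risk would credit some of the shorter observation to the drug.

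Two features add to the problem. First, a responder who is fully weaned in transit and intubated in hospital has the RSI after EOI. Section 7.1.1 says that the risk of severe hypoxia is aggravated during RSI. A fall below 50 at that moment would enter 1.2.2 but not 1.2.4. Second, EOI is defined by INO being discontinued, yet control patients receive none. Section 6.1.2 sets the blender to 20 ppm in both arms with the cylinder left closed in control, while the weaning bullets in 5.3 are written for patients randomized to INO. A control EOI is implied only if the blinded doctor weans the sham setting by the same rule.

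**Working it through.** **Inputs from the protocol.** Starting setting 20 ppm in both arms (6.1.2). Weaning 5 ppm every 5 minutes, begun at t1 if SpO2 is at least 94% (5.3). t1 is minute 5 (section 2). Expected duration about 60 minutes (section 3). 27 patients per arm; SpO2 SD 10 points; planned effect 5 points (10.1).

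**Time of EOI.** 20 ppm / 5 ppm = 4 steps.
- First step at minute 5: 15, 10, 5, 0 ppm at minutes 5, 10, 15, 20, so EOI is at minute 20.
- First step at minute 10: EOI is at minute 25.
- Not weaned early: about minute 60 if the estimated hour includes weaning. If arrival is at minute 60 and weaning starts then, EOI is at minute 75.

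The gap is 60 − 20 = 40 or 60 − 25 = 35 minutes. If the total duration is assumed to be 45 minutes it is 20 to 25 minutes; at 90 minutes it is 65 to 70.

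**Window for 1.2.4.** Early-weaned: 20 − 5 = 15 minutes. Otherwise: 60 − 5 = 55 minutes.

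**Effect on counts.** The documents give neither the event rate nor the share reaching 94%, so both are assumed. Take one constant hazard for all patients, with 15% risk over 55 minutes:
- h = −ln(0.85)/55 = 0.002955 per minute
- risk over 15 minutes = 1 − exp(−15h) = 0.0434
- arm risk = p × 0.0434 + (1 − p) × 0.15, where p is the share reaching 94% at t1

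| Share at 94% (control / INO) | Mean window, min | Risk, control / INO | Risk ratio | Difference in 27 patients |
|---|---|---|---|---|
| 10% / 20% | 51.0 / 47.0 | 0.1393 / 0.1287 | 0.92 | 0.3 |
| 18% / 34.5% | 47.8 / 41.2 | 0.1308 / 0.1132 | 0.87 | 0.5 |
| 30% / 49% | 43.0 / 35.4 | 0.1180 / 0.0977 | 0.83 | 0.5 |
| 30% / 60% | 43.0 / 31.0 | 0.1180 / 0.0860 | 0.73 | 0.9 |
| 40% / 80% | 39.0 / 23.0 | 0.1073 / 0.0647 | 0.60 | 1.2 |

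No drug effect on the events is assumed in any row.

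**Which rows fit the design.** With a normal distribution of SpO2 at t1 and SD 10, a 5-point shift moves the cut-off by half an SD. Control mean 85 gives (94 − 85)/10 = 0.9, or 18%; on INO 0.4, or 34.5%. Control mean 80 gives 8% and 18%, with a risk ratio again of 0.92. A control share of 30% implies 49% on INO, and 40% implies 60% (0.0860/0.1073 = 0.80). The last two rows therefore need an effect larger than the planned 5 points.

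**The case against.** The strongest reply is that little is lost, and much of it stands.

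- **The brake.** A responder at 94% or above who is heading towards 50 first falls more than 5 points from the t1 value. On the rule's wording that interrupts weaning, EOI is not reached, and the event is counted. What is lost is mainly a collapse after complete withdrawal.
- **The hazard.** A constant, equal hazard is doubtful. Patients at 94% are probably at lower risk than those below it, and the protocol places the danger at RSI, which may begin from minute 5. A lower or front-loaded hazard in responders shrinks the artefact.
- **Other capture.** A reader might infer that events after EOI vanish from the trial. They do not. Cardiac arrest is a listed expected SAE recorded in the CRF (8.2.2), and SAEs are collected to day 28 (8.3). Lowest SpO2 at RSI is recorded wherever the procedure takes place (6.1.2), and mortality and GOS-E cover all patients. A late arrest drops out of 1.2.7, not out of the data. No corresponding extraction after EOI is planned for SpO2.
- **The series endpoints.** For 1.2.3, 2.1.1 and 2.1.2 the mixed models named in 10.5 largely deal with series of unequal length, at least where stopping depends on observed SpO2.
- **The analysis plan.** An SAP could add an adjustment for time at risk. It could not recover SpO2 values that were never extracted, and the window itself sits in the protocol's endpoint definition.

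These replies limit the size of the problem. They do not remove the dependence of the window on response in 1.2.4 and 1.2.7.

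**Conclusion.** The point holds for 1.2.4 and 1.2.7. Their observation time depends on a post-randomization response that the drug is intended to change, and the bias runs towards fewer counted events in the better-responding arm. EOI is also not literally defined for control patients.

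The size cannot be read from the documents. Under the equal constant hazard above, plausible shares with the planned 5-point effect give risk ratios of about 0.92 to 0.87. A higher control share moves this to 0.83 at 30% and 0.80 at 40%. In patients this is roughly 0.3 to 0.6 of one event with 27 per arm. A reader might infer ratios of 0.73 or 0.60, but those need a drug effect beyond the planned one. A gap of 35 to 40 minutes is attainable, not typical: it needs uninterrupted weaning and an hour that the protocol itself calls variable.

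Nor does the point reach the main result. The primary endpoint ends at t1 and 1.2.1 ends at ten minutes, and 1.2.2, GOS-E and mortality do not depend on EOI. This is a flaw worth correcting in two secondary endpoints, not a threat to the trial's conclusion on SpO2.

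**What to change.** In sections 2, 6.1.2 and 9.2:

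1. Define 1.2.4 (from t1) and 1.2.7 over one fixed window from allocation, the same in both arms and regardless of blender status. An example is to 60 minutes, the protocol's own expected duration, or to death if earlier.
2. Extend SpO2 extraction to the end of that window, using the monitor trace to handover and the hospital record after it.
3. State how EOI is defined in the control arm.
4. Keep the to-EOI counts as a supplementary on-IMP analysis.

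The cost is amendment wording and a longer extraction from a monitor that already records continuously and from hospital records already listed as source data. The real downside is that some values after handover come from a second source, at a stage when allocation is revealed to the receiving team (10.2) and non-IMP iNO may be used (5.3). The supplementary count shows how much that matters. No change to the weaning rule is proposed.

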### 6.1.4 Follow up visit

Each patient will have data collected in the time from End of Intervention until day 28 after allocation. This will be done by contacting the hospital to which the patient was admitted. A set of questions assessing secondary endpoints and adverse events will be collected and recorded in the database. For patients still admitted to hospital at day 28 the study team will collect the discharge notes from main hospital admission for patients after follow-up visit and prior to end of Trial for SAE data.

### **6.1.5 End of Trial**

End of trial is defined as the last 28 day visit of the last patient

## STUDY PROCEDURE

[figure not shown]

## 6.1.7 Schedule of Activities

| Procedure                                  | Scre
en-
ing |        | Time point (t) |   |   |     |   |   | EOI | E/D | Follow-
up (28
days)                                   | 'Notes

E/D = Early
Discontinuation |
|--------------------------------------------|--------------------|--------|----------------|---|---|-----|---|---|-----|-----|--------------------------------------------------------------|----------------------------------------------|
|                                            |                    | -1     | 0              | 1 | n | RSI |   |   |     |     |                                                              |                                              |
|                                            |                    |        |                |   |   |     |   |   |     |     |                                                              |                                              |
| Eligibility                                |                    |        |                |   |   |     |   |   |     |     |                                                              |                                              |
| -Informed consent                          |                    |        |                |   |   |     |   |   |     |     |                                                              | Variable time point                          |
| - Inclusion criteria                       | X                  |        |                |   |   |     |   |   |     |     |                                                              |                                              |
| - Exclusion criteria                       | X                  |        |                |   |   |     |   |   |     |     |                                                              |                                              |
| Airway intervention                        |                    |        |                |   |   |     |   |   |     |     |                                                              |                                              |
| - PEEP + O 2                    |                    | <===== |                |   |   |     |   |   |     |     |                                                              |                                              |
| - RSI                                      |                    |        |                |   | X |     |   |   |     |     |                                                              |                                              |
| Allocation                                 |                    |        | X              |   |   |     |   |   |     |     |                                                              |                                              |
| Study Intervention                         |                    |        |                |   |   |     |   |   |     |     |                                                              |                                              |
| - INO 20 ppm                               |                    |        | <=====         |   |   |     |   |   |     |     |                                                              |                                              |
| Measurements (endpoint)                    |                    |        |                |   |   |     |   |   |     |     |                                                              |                                              |
| - SpO 2 (1.1.1 and 1.2.1-1.2.3) | X                  |        | X              | X | x | X   | X | X | X   |     | Emergency
unblinding at
doctor's discretion if
< 50 |                                              |
| - BP (1.2.6 and 2.1.2)                     |                    |        | X              | X | X |     | X | X | X   |     | Discontinue if CA                                            |                                              |
| - Respiration rate (1.2.4)                 |                    |        | X              | X | X |     |   |   |     |     |                                                              |                                              |
| - HR (1.2.6 and 2.1.1)                     |                    |        | X              | X | X |     | X | X | X   |     | Discontinue if CA                                            |                                              |
| - EtCO 2 (3.1.3)                |                    |        |                |   |   |     | X | X |     | X   |                                                              |                                              |
| - GOS-E (1.2.7)                            |                    |        |                |   |   |     |   |   |     | X   |                                                              |                                              |
| - Mortality (1.2.8)                        |                    |        |                |   |   |     |   |   |     | X   |                                                              |                                              |
| - Se- urea concentration (2.2.1)           |                    |        |                |   |   |     |   |   |     | X   |                                                              |                                              |
| - KDIGO (2.2.2)                            |                    |        |                |   |   |     |   |   |     | X   |                                                              |                                              |
| - Methaemoglobin (2.3.1)                   |                    |        |                |   |   |     |   |   |     | X   |                                                              |                                              |
| - Platelet count (2.4.1)                   |                    |        |                |   |   |     |   |   |     | X   |                                                              |                                              |
| - Need for INO (2.5.1)                     |                    |        |                |   |   |     |   |   |     | X   |                                                              |                                              |
| - ICD Dx (2.5.2)                           |                    |        |                |   |   |     |   |   |     | X   |                                                              |                                              |
| - O 2 ratio (3.1.1)             |                    |        |                |   |   |     |   |   |     | X   |                                                              |                                              |
| - Se - Cardiac troponin T (4.1.1)          |                    |        |                |   |   |     |   |   |     | X   |                                                              |                                              |
| - ProBNP (4.1.2)                           |                    |        |                |   |   |     |   |   |     | X   |                                                              |                                              |
| Sars COV 19 test                           |                    |        |                |   |   |     |   |   |     | x   |                                                              |                                              |

|                                    |  |  |         |   |  |   |   |   |   |   |  |
|------------------------------------|--|--|---------|---|--|---|---|---|---|---|--|
| Optional Measurements (endpoint)   |  |  |         |   |  |   |   |   |   |   |  |
| - art. blood gas (1.2.5 and 3.1.2) |  |  | X       | X |  | X | X | X | X |   |  |
| - Invasive art. pressure (2.1.2)   |  |  | X       | X |  | X | X | X | X |   |  |
| (S)AE review                       |  |  | <=====> |   |  |   |   |   |   | X |  |
| Concomitant medication             |  |  | <=====> |   |  |   |   |   |   | X |  |

